#### 3.1.3. Parent and Family Focused Qualitative Data

Parents will be given the opportunity to provide feedback about their experience of the FPR program in a semi-structured interview lasting between 30 and 45 minutes. Questions about skills and confidence, parent/child relationships, connection to services, wellbeing, safety and home environment will be asked only to those who choose to participate. The researcher will rely on the expertise of practitioners to engage parents who can speak to their progress. We acknowledge that this approach may lead to confirmation bias, however we feel this is ethically appropriate and is in agreement with MacKillop Family Services staff views. The key worker will provide an explanatory statement and consent form to be completed prior to the interview. It is not a prerequisite that they have signed the consent form for sharing their quantitative measures to complete the interview. The interviews will take place during one of their home visits and the key worker will be there to support the parent pre- and post-interview. Due to COVID-19 pandemic restrictions, geographical distance, and privacy/confidentiality, the interviews will occur over the key worker’s phone or via Zoom, depending on the preference of the parent.

#### 3.1.4. FPR Effectiveness in Reducing Reports to Child Protection and Subsequent Placement into OOHC

To understand if the MacKillop Family Services FPR has been successful at reducing family involvement with child protection and preventing children from entering/re-entering OOHC, three types of linked data from the government are being sourced, subject to approval: (1) reports made to child first, or other child protection organisations who use the Client Relationship Information System (CRIS) system, about FPR children and parents in the six months before participating in the FPR, the six months during and then six months after program closure; (2) number of times children have been in OOHC in the 12 months post FPR participation; (3) time to reunification after removal; or (4) time to removal/re-removal.

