The MacKillop key worker/practitioner engages with the family intensively, defined as a home visit for at least one hour, three times a week, or less visits and regular phone contact plus other activities as required. The timing of these visits is flexible to accommodate the needs of families. Funding is provided to allow for 200 hours of work with an additional 40 hours of step-down towards closure. It is expected that families will engage with the program for approximately six months, but this could last for up to a year. The most practical caseload per full time practitioner is four families, however workers may hold up to six families, albeit at a decreased intensity and with less fidelity to the model. In general, workers focus on reducing stressors and barriers to health and family functioning, such as housing, and offer referrals to specialist services if needed. Workers also focus on the interactions within the family and strengthen core life skills.

For families who are subject to an unborn report (reported to CP while pregnant) or with children aged 0–9, workers use evidence informed methods that focus on parenting skills (i.e., sleep settling, developing routines, responding to cues, use of consequences etc), parent–child attachment, and capacity to effectively respond during a crisis, such as those from the newborn behavioural observation method [20] or circle of security program [21]. These methods support families to meet their goals and mitigate risk. Specifically, the brokerage is a crucial component of the program that helps to fund items that meet families’ immediate or essential needs (i.e., groceries, rent), or can support families to achieve their goals (i.e., fund mental health or substance use counselling). As participation is voluntary and no specific incentives are provided, the brokerage may often be viewed by families as an incentive to engage in the program.

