### 2.3. Participants

There are two participant groups in this study: parents and MacKillop Family Services staff.

Parents: Parents either have children (0–17 years of age) who are vulnerable to removal from the home due to a child protection assessment of risk, have children already in OOHC, or are pregnant and have had ‘unborn’ reports to child protection. These parents may have multiple factors that are contributing to their risk profile including recent family violence, drug or alcohol misuse, fragile mental health, court orders and justice involvement among others. Parents can vary in age and may be adolescent parents or those who are currently living in a care arrangement (foster, kinship, or residential OOHC). Sample size calculations have been conducted using G*Power based on the NCFAS as this measure goes across most efficacy outcomes. For an analysis of variance test with the alpha set at 0.005, correlations between repeated measures set at 0.50 and power of 0.95, a total sample of 98 families will be required. To allow for a 25% rate of non-completion, at least 123 families will be recruited. During the study period, it is expected that up to 1100 families will engage in MacKillop’s FPR program. Based on similar research, we expect a high number of families to consent to participate in the study [25], therefore, it is expected that this sample size requirement will be met by the end of the study period.

MacKillop Family Services Staff: MacKillop directors, managers, team leaders and practitioners involved in the delivery of the FPR program are eligible to participate in interviews or focus groups about their experiences of implementing the program. Only staff who consent will take part in the research evaluation.

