## 4. Analytical Considerations

The primary quantitative outcome of this study is to examine the degree to which there are improvements in psychosocial outcomes among families who engage in the program. All completed questionnaires will be de-identified by a specific data aggregation worker who will assign a unique ID code (e.g., FPR003) to each family so that their data remain anonymous to the research team. Descriptive statistics will be calculated based on administrative and demographic data sourced from the referral form. Main caregiver complexity will be determined using the ACEs survey and the number of ACEs will be calculated. A series of paired sample t-tests (repeated measures) will be used to compare participants’ mean differences on the measures at the beginning and end of the program. Analysis of Variance will be employed to review the number of reports before, during and after the program to determine any statistical differences. The number of care episodes and time to reunification will be analysed descriptively. All analyses will be performed using the Statistical Package for the Social Sciences (SPSS) software.

All qualitative data will be analysed using thematic analysis [41]. Data collection and analysis will occur concurrently so that data saturation can be adequately assessed. All audio recordings will be transcribed verbatim and systematically coded. Following in-depth review of the coded data, independent themes will be identified and developed based on recurrent content reflecting the different aspects of program implementation. The process of refining and reviewing themes will be an iterative process until themes are representative of the most pertinent and recurrent aspects of the data.

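### For children unborn or under six months old at entry, the before window for child-protection reports is not like-for-like with the later windows, yet raw counts are pooled in one ANOVA

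*Protocol article*

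**What the plan says.** Three parts of the protocol article bear on this point.

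- **Windows and what is counted (section 3.1.4).** Linked government data will supply reports "about FPR children and parents in the six months before participating in the FPR", followed by "the six months during and then six months after program closure".
- **Who is in the cohort (section 2.3).** "Parents either have children (0–17 years of age) who are vulnerable to removal from the home due to a child protection assessment of risk"; others already have children in care, "or are pregnant and have had ‘unborn’ reports to child protection". Section 1.2 describes work with unborn-report families and children aged 0–9 as a planned part of the programme, so these families are not incidental.
- **The test (section 4).** "Analysis of Variance will be employed to review the number of reports before, during and after the program to determine any statistical differences". No exposure time, age restriction or separate handling of unborn reports is mentioned.

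Section 4 also says that care episodes and time to reunification will only be described. Reports are thus the only outcome from the linked data for which a test is named.

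**The concern.** A before/after comparison of counts needs the same opportunity for the event in each window. For a child aged six months or more at entry, that holds. For a child unborn at entry, the before window contains no month in which a report about a born child could be made; for a child aged three months it contains three. The after window will normally contain six.

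Selection pulls the other way. A pregnant parent is eligible because an unborn report has been made. If that report falls in the six months before entry, it is in the before count by construction, and the same kind of report cannot recur for that child after birth.

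Neither effect comes from the programme, and an ANOVA on raw numbers cannot separate either from a programme effect. What is at stake is the reading of the one tested measure of reduced child-protection involvement, in a single-group design with no comparison group that would show the same artefact.

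**Working it through.** The plan states no figure on this point, so there is none to reproduce. The check is exposure arithmetic under a constant report rate and no programme effect.

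**From the article:** six months before, six during, six after closure (3.1.4); children aged 0–17 and unborn (2.3); raw counts compared (4).

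**Assumed, because the documents are silent:** share unborn at entry *pu*; share aged under six months *pi*, with an average of 3 months of life; report rate *r* per child-month after birth; one unborn report per unborn case when counted; birth before closure, so that the after window is full.

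**1. One child.** Months since birth in the before window = min(age at entry, 6). After/before ratio with no effect:
- 1 month: 6/1 = 6.0
- 2 months: 6/2 = 3.0
- 3 months: 6/3 = 2.0
- 5 months: 6/5 = 1.2
- 6 months or older: 6/6 = 1.0
- unborn: 0 against 6 months, so no ratio exists

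**2. Whole cohort, child reports only.** Before child-months per child = (1 − pu − pi) × 6 + pi × 3.
- 5% / 5%: 5.40 + 0.15 = 5.55; 6/5.55 = 1.08
- 10% / 10%: 4.80 + 0.30 = 5.10; 6/5.10 = 1.18
- 20% / 15%: 3.90 + 0.45 = 4.35; 6/4.35 = 1.38

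**3. Adding parent reports at the same rate.** Parents contribute six full months to each window, so 6 is added above and below:
- 12/11.55 = 1.04
- 12/11.10 = 1.08
- 12/10.35 = 1.16

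The apparent rise falls to a little under half.

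**4. Counting the unborn report, 10% / 10% mix, no parent reports.** Before = 5.10r + 0.10; after = 6r.
- r = 0.05: 0.255 + 0.10 = 0.355 against 0.300, a change of −15%
- r = 0.20: 1.02 + 0.10 = 1.12 against 1.20, a change of +7%
- The sign changes where 0.90r = 0.10, at r = 0.11 per month

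Within unborn entrants alone, after/before = 6r/1: 0.30 at r = 0.05, 0.60 at 0.10, 1.5 at 0.25 and 2.4 at 0.40.

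**5. The during window.** A child born *b* months into a six-month during window has 6 − b months there; for b = 2, 4 months. For such a child, time since birth differs across all three windows (0, 4, 6), not only between before and after.

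**The case against.** The strongest reply is that the plan counts family involvement, not child events. Section 3.1.4 includes reports about parents, section 4 assigns one code per family, and section 2.3 sizes the study in families. Parents and older siblings can be reported throughout the before window, and an unborn report is itself a report to child protection. This stands in part. It shows that the before window is not empty and that the figures in step 2 are upper values for their assumed mixes. It does not make the windows equal: step 3 leaves 4% to 16%, and a family-level count still gains a newly reportable child and still includes the entry report.

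A reader might infer that in infant families the before/after difference reflects birth rather than the programme. The documents do not support that. Birth is one influence among several, and its size and even its sign depend on rates that are not given. Nor should 38% be read as an estimate; it follows from one assumed mix.

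It can also be said that exposure definitions belong in an analysis plan that is not shown, that section 4 names psychosocial improvement as the primary quantitative outcome, and that section 2.2 admits limitations of the design. The first is possible, but the article itself fixes the windows, population and test, and these three do not fit together. The second lowers the weight of the point. The third is general and does not cover a definition that can be repaired.

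**Conclusion.** The point holds in a limited form. For children unborn or under six months at entry, the before window is not comparable with the later ones, and pooling raw counts mixes a birth and selection artefact into the test of reports. For children aged six months or more at entry, before and after child time is equal and the point does not arise.

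Under the assumed 5–20% unborn and 5–15% under six months, the artefact across the cohort is about +8% to +38% for child reports alone and about +4% to +16% with parent reports at the same rate. For the 10% / 10% mix with one unborn report counted and no parent reports, it runs from −15% to +7%. All of these rest on a constant report rate and assumed shares; the documents fix neither size nor direction. The change is worth making before the linked data are analysed, because the coding of unborn reports can decide the sign of the result in this group.

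**What to change.** In sections 3.1.4 and 4:

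- Count three things separately: reports about parents, reports about born children, and unborn reports.
- Analyse reports about born children with child-months since birth in each window as the exposure, including the partial during window of a child born in the programme. Parent reports need no such denominator and can be compared over the full windows.
- Keep all families in the main comparison. Show families entering on an unborn report, or whose only child is under six months at entry, as a separate stratum.
- Repeat the before/during/after test without that stratum as a sensitivity analysis.

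The cost is somewhat more analysis and lower precision in the restricted test. The evaluators also need child age in months at entry and, for children born during the programme, the month of birth relative to entry. The service already uses age in months to choose the ASQ form (section 3.1.2). Consent covers the assessments and limited non-identifiable demographic data (section 2.4), so whether sharing age in months falls within it should be confirmed.

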In June 2020, a tender was put out requesting submissions from suitable community service organisations across Victoria who deliver family services to vulnerable families. Seventeen tenders were released to deliver the program across sites in both urban and regional settings. The goal of the Response was stated as being “strong families-with children who are safe, healthy, resilient and thriving; and parents who are supported to create a safe and nurturing home environment” [15]. The program seeks to provide intensive support to families where the children are at significant risk of being removed and placed in OOHC, or to enable the reunification of removed children in a timely manner. Referrals into the program are made via Child Protection, yet participation is voluntary. The FPR model is premised on the assumption that early, targeted and intensive support will permanently change the trajectory of vulnerable families away from the child protection (CP) system and towards the self-management of needs. OOHC placement often has adverse impacts on the child and family, and is extremely costly [16]. Hence, from a social, emotional and economic perspective, it is much better if families are supported and strengthened to ensure children can stay at home, safely. Table S1 outlines the government-led, individual core components of the Victorian FPR Response. Many are unique compared to other intensive family services by, for example, targeting adolescents, having a focus on implementation science (i.e., exploring *how* the program is being delivered), significant brokerage (i.e., funding to be used to purchase necessities for the family, such as groceries, housing appliances, contribute to rent, medication etc) and a new role within child protection called a Navigator. The Navigator is a government position that has been established within child protection to ensure that coordinated, targeted, appropriate, and culturally safe referrals are made into the FPR program. Rather than being prescriptive in program design, the Victorian government allowed all community service organisations to propose their own version of the FPR Response (within some broad parameters), with the view that consistency will be embedded through the government’s delivery of training and coaching to common practice elements (i.e., core components of program delivery) [17]. MacKillop Family Services was awarded nine areas of Victoria (six urban and three regional) to deliver the program.

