Families enter the program via the CP navigator. The navigator supports child protection practitioners to identify, engage, and connect the most appropriate families into the FPR program. Known as a ‘connection’ (i.e., referral or handover), the child protection practitioner, the Navigator, and MacKillop team leader discuss the family members, their circumstances, and past-history, prior to MacKillop accepting the family into the program. In alignment with collaborative practice and the two mandated Information sharing schemes (Child Information Sharing Scheme and Family Violence Information Sharing Schemes) [18,19], CP share all information relevant to the health and safety of the family and their workers. This includes mandated policy documents such as the Multi-Agency Risk Assessment and Management (MARAM) family violence screening and cultural support plans for Aboriginal and Torres Strait Islander children, as well as other known reports, such as mental health or disability assessments. Upon acceptance, MacKillop make contact within 48 hours and visits the family with CP within seven business days. These timeframes were prescribed by the Department of Family, Fairness and Housing. A thorough assessment of child and family outcomes is undertaken, and a ‘child and family action plan’ (i.e., care plan) is completed within 3 weeks that comprises the family’s goals, which are informed by those of CP. The plan is a living document that is revisited regularly to monitor progress and add or revise goals. CP workers are kept abreast of the family’s progress through attendance at care team meetings that are chaired by MacKillop Family Services workers.

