The program is also designed to support families to link into the community and its services to build independence, self-sufficiency, and a social network. Multi-disciplinary teams forged through partnerships with other agencies enhances the direct engagement of families with experts in parenting, drug and alcohol services, as well as regional care. Once families are better placed to meet the challenges they face and preferably with achieved goals, MacKillop will close the connection, but not before they provide the families with referrals to other programs or services if needed. For some families with young children, and where agreed to by the CP Navigator, an additional episode of care (240 h) will be provided to ensure that the family’s capacity is sufficient to keep children safe and thrive.

Families in metropolitan areas with young people aged 10–17 years engage with the evidence based Multi-Systemic Therapy Psychiatric (MST-Psych) program [22,23] where they see a trained MST-Psych MacKillop worker (termed family therapist) for at least one hour, three times a week. Full time family therapists are expected to hold up to four families and be available after hours where necessary. Family therapists adopt a systems approach by working closely with the child as well as the systems in which they live, e.g., caregiver, broader family members, home environment, school, peers, and community. They implement a range of evidence-based interventions, such as behavioural therapy, parent management training, cognitive behavioural therapy, and family therapy to meet the treatment goals within each system before closure. The regional MacKillop FPR programs also work with families of this age group, however they do not deliver an approved MST-Psych program, rather, they offer a service informed by this expertise.

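### The before/during/after comparison of child-protection reports can shift because the programme changes how concerns are detected and routed in the during window, in a direction the documents do not settle

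*Protocol article*

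**What the plan says.** Section 3.1.4 of the protocol article uses linked government data to judge whether the programme "has been successful at reducing family involvement with child protection and preventing children from entering/re-entering OOHC". One of the linked items is the count of child-protection reports about participating children and parents "in the six months before participating in the FPR, the six months during and then six months after program closure". Section 4 fixes the test: "Analysis of Variance will be employed to review the number of reports before, during and after the program to determine any statistical differences". Table 1 also lists child-protection notifications under family safety and home environment, so the count is meant to speak to safety as well as to service contact.

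The article also describes who sees the family in each period:

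- **Entry.** "Referrals into the program are made via Child Protection, yet participation is voluntary" (Section 1.1).
- **During.** Intensive engagement means "a home visit for at least one hour, three times a week, or less visits and regular phone contact" (Section 1.2). Child Protection is kept informed "through attendance at care team meetings that are chaired by MacKillop Family Services workers". "Multi-disciplinary teams forged through partnerships with other agencies enhances the direct engagement of families with experts" (Section 1.2).
- **Closure.** The provider ends the connection and refers families onward where needed (Section 1.2).

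Section 2.2 rules out any control group and acknowledges the limits of the pre-post design in general terms. It does not mention changes in how reports come to be made.

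**The concern.** A report exists only if somebody sees a concern and lodges it. The programme puts workers and partner agencies in contact with the family, and gives the worker a direct channel to Child Protection. Both features belong to the during window. The intervention therefore alters the measurement process of one of its own outcomes, in one of the three periods being compared.

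Two mechanisms are plausible and they pull in opposite directions. Workers who see more may lodge more reports, which raises the during count. Alternatively, a concern may be dealt with at the care-team meeting with no fresh report, which lowers it. In a controlled design some of this could be netted out; here it cannot. What is at stake is whether a significant ANOVA on these counts can be read as a change in the family's circumstances. Section 6 says that significant improvements would strongly support wider roll-out.

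**Working it through.** The article gives no report rate and no figure for detection, so there is no stated result to reproduce. The check has three steps.

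**1. Observation by window, from the article's own description**

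| Window | Programme contact | Other observation described |
|---|---|---|
| Six months before | None | Family already known to Child Protection, which refers it (Sections 1.1 and 1.2) |
| Six months during | Home visits or phone contact, care-team meetings, partner agencies (Section 1.2) | Child Protection remains involved |
| Six months after closure | None once the connection is closed | Other services, for families referred on |

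At full intensity the during window holds 3 visits × 26 weeks = 78 visits. Section 1.2 allows fewer visits supplemented by phone, so 78 describes full intensity and is not an expected average.

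**2. What a detection change does to the count**

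Let the expected count in a window be H × d, where H is harm (held constant) and d is the chance that harm produces a report. Set d = 1 before and after. The shares below are assumptions; the documents give none.

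- *Workers add a share a of reports:* during/before = 1 + a. For a = 20% to 50%, the during count is 20% to 50% higher. The fall at closure is 1 − 1/(1 + a): 1 − 1/1.2 = 17% and 1 − 1/1.5 = 33%.
- *A share r is handled without a report:* during/before = 1 − r. For r = 20% to 50%, the during count is 20% to 50% lower. The rise at closure is 1/(1 − r) − 1: 1/0.8 − 1 = 25% and 1/0.5 − 1 = 100%.
- *Both act and multiply:* they may cancel. With a = 25% and r = 20%, 1.25 × 0.8 = 1.00.

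In all three cases the before-to-after ratio stays at 1.

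**3. Could such a shift reach significance?**

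A one-group repeated-measures ANOVA was simulated on Poisson counts with a gamma family effect (shape 1), equal harm in all windows and 1,500 runs per setting. N = 98 is the required sample in Section 2.3. It was derived there for the NCFAS and is used here only for scale. Mean counts and detection ratios are assumed.

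| Detection before : during : after | Level | Mean 0.5 reports | Mean 1 | Mean 2 |
|---|---|---|---|---|
| 1 : 1 : 1 | 0.05 | 4.0% | 5.5% | 5.3% |
| 1 : 1.25 : 1 | 0.05 | 20.9% | 38.7% | 66.4% |
| 1 : 1.5 : 1 | 0.05 | 63.7% | 91.9% | 99.5% |
| 1 : 1 : 0.75 | 0.05 | 22.7% | 45.7% | 76.9% |
| 1 : 1.5 : 1 | 0.005 | 29.2% | 64.7% | 96.5% |

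Entries are the proportion of runs with a significant result although harm did not change. A lower detection rate in the during window was not simulated. The table shows that a moderate detection change would be enough to produce a significant difference; it does not show that one occurs in this study.

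**The case against.** The strongest reply has four parts.

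**Direction.** A reader might infer that the drop from during to after is biased towards success, because the programme's observers leave at closure. The documents do not support that. It follows only if workers mainly lodge reports. If concerns mainly go through care-team meetings, the during count is too low, and the same contrast is biased the other way. The sign is unknown.

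**Contrast between windows.** Families are not unobserved outside the programme. Child Protection already knows them before entry, and onward services may see them afterwards. Section 1.2 also funds 40 step-down hours towards closure, so contact need not stop abruptly. This stands, and it confines the point mainly to the during window.

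**Silence is not a rule.** A reader might also infer that the plan pools all reports regardless of who made them or whether they were upheld. Neither Section 3.1.4 nor Section 4 says so, and the article condenses a fuller plan that is not shown. The point rests on the three-window comparison that is stated, not on missing field definitions.

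**Consequence.** Section 4 names psychosocial improvement as the primary quantitative outcome, out-of-home-care placement is measured alongside reports, and Section 5 claims only some conclusions about potential impact. This limits the weight of the point. It does not remove it, because the reports are offered as evidence of success and are formally tested.

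**Conclusion.** The point holds in limited form. The planned ANOVA includes a window in which the programme itself changes both detection and routing of concerns, with no control group. The during count can move either way with no change in harm. Direction and size cannot be obtained from the documents; the 17–33% and 25–100% figures restate assumed shares, and the simulated rates depend on assumed ratios and mean counts.

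The before-versus-after contrast is the sounder one for this issue, because no programme worker is in the home in either window. That assumes that closure marks the end of the last episode, since some families may receive a further 240 hours. The contrast keeps a separate weakness: entry by Child Protection referral may make the before count high by selection. It should not be presented as free of bias.

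This is a worthwhile, inexpensive improvement to one of several effectiveness outcomes, not a defect that undermines the study.

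**What to change.** 1. In the linked-data request, which still awaits approval, ask for two further fields per report: reporter type and substantiation status.
2. Keep the all-source count as the analysed quantity. Beside it, for each window, report counts split by source (programme staff versus others) and the substantiated count.
3. Base the effectiveness reading on before versus after. Do not interpret a change into or out of the during window as a programme effect unless it also appears in the source-restricted and substantiated counts.

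Two tempting additions should be avoided. Replacing the tested count with reports from outside the programme would discard real harm that workers saw, in the during window only. Adding care-team concerns from case notes would bring in a source that exists in that window alone.

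The cost is two more data fields, if the extract holds them (the documents do not say), with fewer events and wider intervals in the restricted counts.
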